Emergency management is an integral part of primary care. As a primary care provider, primary care workers can be confronted with any type of emergency that requires updated knowledge, communication and manual skills, trained personnel, appropriate equipment and practice organization, and necessary medication. The wide range of symptoms and the rarity of situations make it difficult for primary care staff to keep up to date and be competent in life support [12]. The use of new training methods, such as classroom simulations with 3-dimensional (3D), highly realistic simulators [13] or in situ simulations, can provide comprehensive training in handling medical emergencies and identifying potentially dangerous medical situations that are not part of the daily work of primary care physicians and other health care workers [14].

Despite the growing body of evidence that AR is effective in medical education, some studies failed to confirm this, reporting no significant impact of the use of AR on learning and no differences according to device used (mobile or other) [15].

There are also several disadvantages of AR use for medical education that could be important, such as the possibility of deteriorating human connections; technical problems, which could affect the learning process; lack of privacy during learning; and questionable cost benefit.

The primary objective of this study is to evaluate the short-term and long-term effectiveness of the use of AR in the management of patients with anaphylactic shock. The secondary objectives are to assess the safety in the treatment of patients with anaphylactic shock, evaluate the short-term and long-term effectiveness of stress management in this process, and determine the experiences and viewpoints of participants regarding the use of AR in education.

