**Figure 1 figure1:**
[figure not shown]
Schematic presentation of the randomized controlled trial in phase two of the study. WCQ: Ways of Coping Questionnaire.

After the intervention (see Intervention), the participants will once again perform the simulation with a high-fidelity simulator and complete the WCQ, which will be followed by a debriefing. We will use a structured tool for debriefing called TALK (Target, Analysis, Learning Points, Key Actions), which is designed to guide structured team self-debriefing after any learning event in clinical environments. It promotes a supportive culture of learning and patient safety [23]. The simulations will be again video recorded, and the recordings will be assessed by experts as already described.

Both groups will be assessed again at 1 month and 1 year after the intervention, using the WCQ scale and simulation. This time, the simulation will be performed in the participant’s workplace and with a standardized patient, followed by a debriefing. The scenario of the simulation will be the same as before. Again, simulations will be video recorded; experts, as already described, will assess the recordings.

The short-term effect will be measured using performance immediately and 1 month after the intervention, while the long-term effect will be measured 1 year after the intervention, which will also be our primary time point.

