### Statistical Analysis

#### Power Calculation

Sufficient sample size to detect a difference between the test and control groups in the score of the evaluation scale (primary outcome) using a 2-tailed independent *t* test was determined using power analysis. For α of .05 and 80% power to reject the null hypothesis of equal group means, when the population mean difference is 10 points (considered clinically relevant) and population SD of both groups is 20 points, a sample size of 128 (64 per group) is needed. The SD of 20 was used based on the results of a study on the use of case-based simulations with high-fidelity mannequins in teaching and retention of emergency management team skills [18]. In that study, the SD of the evaluation scores was <20 for all scenarios. To account for dropouts, we plan to recruit 150 participants.

For the secondary outcome (dichotomous version of the score of the evaluation scale), we performed power analysis using the planned sample size of 128 (64 per group). A chi-square test with α of .05 achieves 80% power to reject the null hypothesis of equal group proportions of successful assessments if the population difference between the group proportions is 21%-25%, where the proportion of successful assessments in the control group is assumed to be between 15% and 40%.

Sample size calculations were conducted using PASS 2019 Power Analysis and Sample Size Software [24].

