#### Statistical Methods

We will summarize categorical variables with frequencies and percentages, and we will summarize numerical variables with means and SDs or medians and IQRs in the case of asymmetric distributions. To highlight the differences between the groups at baseline, we will use the chi-squared test or Fisher exact test (if more than 20% of the expected frequencies are below 5) for categorical variables and independent samples *t* test or Mann-Whitney U test (in the case of asymmetric distributions) for numerical variables.

For the comparison of groups after 1 year (primary time point), we plan to use a *t* test for independent samples (or Mann-Whitney U test) for the evaluation scale score (primary outcome) and a chi-squared test (or Fisher exact test) for its dichotomous version (secondary outcome) and for the safety criteria. To compare groups at all time points (right after the intervention, after 1 month, and after 1 year) efficiently in one model, we will use appropriate mixed-effects regression models, which are able to appropriately take into account repeated measurements of the same patient. The power for detecting differences between groups with these models is even higher than with independent *t* tests or chi-square tests that were used in the power analysis.

To evaluate the short-term and long-term effectiveness of coping with stress, only the following dimensions will be included in the analysis: confrontation, distance, self-control, seeking social support, taking responsibility, escape/avoidance, planned problem solving, and positive reassessment. We will sum items to provide each of these scales. For each scale, groups will be compared using a linear mixed-effects regression model.

A *P* value <.05 will be considered as statistically significant.

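### The 1-year primary test is protected, but eight WCQ scales are each tested at an unadjusted .05, giving about a 19%-34% chance of at least one false stress finding

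*Protocol article*

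**What the plan says.** The Statistical Methods section of the protocol article lists eight WCQ dimensions, forms a sum score for each, and states: "For each scale, groups will be compared using a linear mixed-effects regression model". The section closes with the only significance rule in the document: "A *P* value <.05 will be considered as statistically significant". Nothing there limits that rule to the primary test.

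The WCQ is completed at baseline, right after the intervention, at 1 month and at 1 year (Procedures and Data Collection, Phase Two). It serves a secondary objective, which asks about stress management in both the short and the long term (Introduction).

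The main comparison is fixed clearly. Measures names the percentage score as the primary outcome, Phase Two names 1 year as the primary time point, and Statistical Methods gives the test at that time. Power Calculation sizes the trial for this outcome: "For α of .05 and 80% power to reject the null hypothesis of equal group means".

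The objective is worded more widely than this comparison: "The primary objective of this study is to evaluate the short-term and long-term effectiveness of the use of AR in the management of patients". Phase Two adds: "The short-term effect will be measured using performance immediately and 1 month after the intervention".

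**The concern.** Eight scales together answer one question, whether AR training changes how physicians cope with stress. Under the stated rule each scale has its own 5% chance of a false positive, and the article does not say how many scales, or which, must be significant for the question to be answered. A report that follows the rule can therefore present one scale out of eight as a significant effect on coping when the intervention has none. If each follow-up visit is read separately, there are more such chances.

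What is at stake is the credibility of the stress findings, not the main conclusion on performance. A smaller ambiguity is that the primary objective covers short and long term while the primary time point is 1 year alone. A reader could be unsure what standing the immediate and 1-month performance results have.

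**Working it through.** **Inputs from the protocol.** Threshold .05 for all analyses and eight WCQ scales, one model each (Statistical Methods). Three post-intervention visits (Statistical Methods; Phase Two). 64 per group, difference 10 and SD 20, a standardized difference of 10/20 = 0.5, tested "using a 2-tailed independent" t test (Power Calculation).

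**Assumed.** The protocol gives no correlation between WCQ scales or between visits. Equal correlations between scales and between visits were assumed and varied.

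**Step 1: the protocol's own figure.** The inputs are stated as "when the population mean difference is 10 points (considered clinically relevant) and population SD of both groups is 20 points". The normal approximation gives n per group = 2 × (1.960 + 0.842)² × (20/10)² ≈ 62.8, so 63. The exact noncentral t solution is 63.77, so 64 per group and 128 in total, with 80.1% power. The stated 128 is reproduced. It rests on one comparison at .05, so the primary test has a 5% error.

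**Step 2: eight scales, one test each.** The expected number of false positives is 8 × .05 = 0.4, whatever the correlation. The chance of at least one, if the scales are independent, is 1 − 0.95⁸ = 33.7%. With correlated scales (400,000 multivariate normal draws, two-sided .05):

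| Between-scale correlation | At least one of 8 significant |
|---|---|
| 0 | 33.7% |
| 0.3 | 29.9% |
| 0.5 | 25.0% |
| 0.7 | 19.2% |

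**Step 3: eight scales at each of three visits.** If all 24 tests are independent, 1 − 0.95²⁴ = 70.8%. Independence between visits in the same people is not realistic, so both correlations were varied by the same method:

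| Between-scale correlation | Between-visit 0.3 | 0.5 | 0.7 |
|---|---|---|---|
| 0.3 | 63.8% | 60.5% | 55.1% |
| 0.5 | 56.0% | 52.8% | 47.5% |
| 0.7 | 45.2% | 42.2% | 37.3% |

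**Step 4: the performance score, for contrast.** Read at 1 year only, the error is 5%. Read as a success at any of the three visits, it is 1 − 0.95³ = 14.3% if independent, and 13.6%, 12.6%, 10.9% and 8.3% at between-visit correlations of 0.3, 0.5, 0.7 and 0.9.

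**Step 5: the price of adjustment.** Holm's first step over eight tests uses .05/8 = .00625. For a single comparison with 64 per group and an illustrative true difference of 0.5 SD on one scale only, power falls from 80.1% at .05 to 52.1% at .00625.

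**The case against.** A reader might infer that a false claim of effectiveness is likely for the trial as a whole. The documents do not support that. One outcome, one time point and one powered comparison carry the main conclusion, and that test is not inflated. Even a loose reading of the score at any visit reaches only about 8%-14%.

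A reader might also infer that the written rule gives more than even odds of a false WCQ finding. That requires a separate test at each visit, which the text does not specify. It commits to eight models and does not say whether each yields one overall group comparison or three. Even with 24 tests the range runs from 37% to 64%, so even odds are not assured. On the other side, one overall test per scale could not separate short-term from long-term effects, which the objective asks for, so eight tests is the low count.

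Nor does the protocol say that one significant scale in either direction proves effective coping. If only favourable results are counted, the chance is about 10%-18% for eight tests and 19%-36% for 24. This lowers the practical risk but does not remove it.

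Finally, the WCQ is secondary and a condensed article may leave detail to an analysis plan. That is fair for the direction of benefit on each scale and for what happens if the two short-term visits disagree; neither is held against the protocol here. It does not dispose of the blanket .05 sentence, which the article itself states and which an analysis plan would have to override.

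**Conclusion.** The point holds for the WCQ analyses only. Following the stated rule, the chance of at least one falsely significant scale is about 19%-34% with one test per scale and about 37%-64% with a test at each visit. These figures assume no true effect on any scale, two-sided tests and the correlations shown, none of which the protocol supplies. The per-visit range also assumes a testing pattern that the protocol leaves open.

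The primary 1-year comparison stands as planned. The mismatch between a primary objective covering both periods and a single primary time point does not inflate that test; it needs one clarifying sentence. Overall this is an inexpensive improvement to a secondary analysis, not a threat to the trial's main result.

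**What to change.** Change Statistical Methods in one of two ways:

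- Apply Holm across the eight 1-year WCQ contrasts, and report the WCQ results at the other visits as estimates with 95% confidence intervals and no significance claims; or
- Label all WCQ analyses exploratory, so that the .05 rule does not support a claim on them.

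In either case, add that the immediate and 1-month comparisons of the performance score are secondary to the 1-year test. A fixed testing order starting at 1 year would also control the error for the score, but it would bar any short-term claim if 1 year fails. The protocol itself expects skills to fade without practice (Discussion, Methodology), so that is a choice for the sponsor and not a necessary correction.

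The cost is wording only, with no effect on the primary test or on N=128. Holm does cost power for a lone WCQ effect, about 80% to 52% in the 0.5 SD illustration at its first step, on scales that the trial was not powered for. The exploratory label avoids that loss but gives up a confirmatory claim on stress.

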### Qualitative Analysis

We will perform a thematic analysis following a semantic approach. We intend to get the explicit opinions of the participants on their experiences with education using AR. We do not want to study the underlying assumptions and beliefs that are rooted in the context of the interviews we will perform. The thematic analysis is, according to Guest et al [25], the most useful data analysis technique in capturing the complexity of data within qualitative data and offers a valuable approach for applied research [26]. Thematic analysis is an “organic approach” [27] to coding and generation of the themes that allow for in-depth exploration of the experiences, beliefs, and views, providing a comprehensive understanding of the knowledge that participants had with AR in education. 

The inductive approach in this study will enable researchers to develop a thematic framework emerging from the data (“from the ground up”). A semantic approach will be used since our goal is to explore participants' experiences, beliefs, and views. 

The analysis will be comprised of 6 stages: (1) getting familiar with the data while reading the transcript, (2) generating initial codes, (3) generating themes based on the codes, (4) reviewing initial codes and re(combining) them into previous or new themes, (5) developing and defining names of the themes, and (6) reducing the number of themes into a more manageable set of important themes [27].

We will use NVivo Pro 11 software V.11, 2015 to code the data for the thematic analysis, generate codes and categories, and increase the accuracy of the working methods and result [28]. We will treat data from every stage collaboratively and corroboratively. Multiple researchers from the team will code the data and confirm thematic analysis to ensure that the researcher's perspective does not bias the data's interpretation. This will ensure that the working methods are trustworthy and valid (investigator triangulation). 

## Results

We developed a scenario for simulation with a high-fidelity simulator and standardized patient (Textbox 1). We are currently developing an evaluation scale and starting to recruit participants. We are planning to finish participant recruitment by the end of December 2020, while the main trial will start in January 2021 and finish a year later. The first results are expected to be submitted for publication in 2021.

Scenario for simulation with a high-fidelity simulator and standardized patient.The patient is an otherwise healthy 32-year-old woman with no known history of allergy who received an intramuscular injection of ketoprofen due to back pain. Within minutes, the patient showed signs and symptoms consistent with anaphylaxis, and the participant should quickly take a specific history and physical examination and begin treatment. If the correct diagnosis and treatment are made, the patient will improve. If the participant does not recognize that the patient is in anaphylaxis or is only administering second-line therapy without epinephrine, the patient deteriorates into respiratory arrest with pulseless electrical activity and requires resuscitation according to Advanced Cardiac Life Support (ACLS) guidelines.

## Discussion

### Expected Results

This will be the first study to evaluate the effect of using AR for teaching in an urgent primary health care situation. The main outcome of this study will be the short-term and long-term effectiveness of the use of AR in the training of primary care physicians. We expect that the participants who are trained with AR in addition to the standard training will achieve better results in the treatment of a patient with anaphylactic shock in the simulation compared to other participants.

Several systematic, scoping, and integrative reviews on the use of AR in medical education showed that, while AR technology is growing at a rapid rate, the current quality and breadth of AR research in medical training are insufficient to recommend its adoption into educational curricula [2-4,29]. Existing studies mainly focus on the evaluation of prototypes instead of long-term studies. There is a lack of evidence for the implementation of AR in medical education [8], including training in emergency care [9], even though some studies demonstrated its effectiveness [2,11]. Therefore, we expect that our study will fill the gap on the effectiveness of AR in medical training and provide new insights into its short-term and long-term effects.

Our additional outcome will be the evaluation of safety in the treatment of patients with anaphylactic shock. We expect that participants trained with AR will treat their patients more safely than participants who are not trained with AR. With the use of AR in teaching, we also reach participants who have never seen a patient with anaphylactic shock before. Training with AR enables comprehensive training in dealing with medical emergencies on the one hand and in recognizing potentially dangerous medical situations on the other. This approach also enables us to determine the quality of work and identify potential safety risks in the treatment of patients. We will also evaluate the short-term and long-term effectiveness of stress management in dealing with patients with anaphylactic shock. Stress is widely present in medicine, particularly when dealing with urgent situations [10]. As stress hampers the ability to perform work safely and to achieve a high standard of quality [4], it is important that doctors are educated early on how to manage stress [10]. With AR simulations, we can replicate real patients to reflect real situations in the clinical environment [12] and compare the knowledge of different teams. This provides a safe way to learn how to deal with difficult, unusual, or serious clinical situations. The scenarios are standardized and at the same time flexible, which allows for adaptation to the level of competence of the trainees. The training process is uniform and standardized, which promotes a high quality of learning and does not require years of exposure at accident sites. Realistic, stressful scenarios using highly realistic simulations promote simulated learning, where primary health care teams can interact with patients. Participants learn how to deal with stress during a simulation and manage the patient independently. They can safely explore their feelings and fears and learn how to face and overcome them [13].

With the qualitative part of the study, we want to find out about the experiences with this kind of training, the attitudes toward this teaching method, and suggestions for improvement. We also expect to identify the strengths and limitations of this novel and innovative teaching approach.

### Methodology

The main methodology of this study will be a single-blinded RCT using the AR intervention. We chose AR technology over VR technology because AR allows virtual presence to be blended into the users’ reality with minimal interference. Therefore, we will create a more realistic environment compared to VR, which will allow the training of users in their working environment.

In addition, we will use a qualitative methodology. With such a methodology, we want to prove the validity of our AR application for education or training of medical professionals. According to Barsom et al [3], it is important to focus on 5 levels of validity. Face validity (ie, the degree of similarity between the AR application and the training construct) will be evaluated with focus groups. Content validity (ie, the degree to which the content of the AR application covers the dimensions of the medical content) will also be evaluated with focus groups. The other 3 levels will be assessed through the RCT: (1) construct validity (ie, inherent differences in outcome between experts and novices on outcome parameters relevant to the educational construct), (2) concurrent validity (ie, concordance of the subject's outcome parameters using AR compared to the outcome parameters of an established instrument or method that is assumed to measure the same educational construct), and (3) predictive validity (ie, the degree of agreement between the outcome parameters of AR and the respondent's performance goals, which are supposed to be similar in reality). With the qualitative part of the study, we also want to address the possible downsides of the use of AR in medical education that have already been reported in previous studies [15].

The evaluation of performance will be conducted with a simulation, first in the training environment with a high-fidelity simulator and later in the clinical environment with a standardized patient. With such methodology, we will meet the criteria for translational research [5] using 3 stages: (1) evaluation of performance in the educational environment, (2) evaluation in the clinical environment, and (3) evaluation in health care, community involvement, and prevention services. This study will show the possibility of using AR education for actual clinical practice.

There are some drawbacks of simulation in health care. Simulation relies on space, time, equipment, and skilled human resources. Setting up and running the simulation can be expensive [30]. The simulation center where the study will be conducted is an already established and active center with many simulation trainings conducted over previous years [14]. Therefore, we are certain that these drawbacks will be handled appropriately. Another problematic issue in simulation might be the need for an adaptation period for students to perform the simulation. It is mainly during the second simulation that a student will really start to be able to adapt and treat the patient simulator more realistically [30]. We are aware that this could affect the results of our study, but given the fact that all participants will have the same conditions, we think that this drawback will also be handled appropriately.

In education at all levels and in all fields, studies usually focus on short-term results, assessing the outcome during or immediately after the time when the education took place. Unfortunately, it is true that mastery demonstrated during or immediately after learning can easily be lost in the weeks and months that follow without continued practice [6]. Therefore, in this study, we have chosen to evaluate the short-term and long-term effects by assessing performance immediately after the intervention and 1 month after, given that short-term performance is a good predictor of performance over longer periods of time, and 1 year after the intervention (long-term effect). The long-term preservation of knowledge is the most important, as it is an indicator of permanent memory.

